### Handling of protocol non-adherence and missing data

The way the questionnaires are administered online makes it impossible to skip a question. Participants who do not complete a questionnaire will receive one or more reminders. Missing data during observations is also not possible. Missing data during the follow-up period (e.g., due to unavailability during a certain measurement wave or due to dropout) will be handled using Full Information Maximum Likelihood (FIML) estimation.

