Summed scores will be computed for each girl that are the total number of responses of each type that the adolescent produce. The decision to use summed scores for the analyses (as opposed to proportion scores, i.e., the percent of responses of each type out of the total number of responses) is based on the idea that the total number of experiences that adolescents have in which they hear positive engaged, negative or humorous response statements (in other words, the cumulative experience of hearing these responses) should have a particular critical influence on friendships.

Finally, all the problem-focused thought units will then be assigned one of the topic codes. The topic codes were generated a priori based on the literature reviewed regarding challenges during adolescence. Three topic codes are interpersonal: family, peers (nonromantic), and romantic interests. Three are not interpersonal: academics, athletics and other extra-curricular activities, and jobs and money. Finally, each problem-focused thought unit will be timed. The number of seconds that friend dyads spent on each problem topic will be summed. For each step, 25% of the dyads will be double coded. Interrater reliability will be computed separately for T0 and T4.

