#### Negative and serious adverse events

##### Participation in the PTT

In advance of the PTT, parents/main caretakers will be asked to stay at home during the online measurements to assist their daughter and provide support if needed. During the PTT, the trained researchers and research assistants will adhere to the Code of conduct for resistance in minors and the Observation protocol. Girls will also be told that they are free to withdraw from the task at any time, without further consequences. They will also be told that all information they share during the PTT will be treated confidentially, but that the researchers should terminate the task when there are doubts about the safety of the participants and that, in that case, parents/main caretakers or school professionals will be informed (see below for details). Girls will be informed that this will be the case when they talk about suicide, self-injury, sexual or physical abuse, substance abuse, or eating disorders during the task. Girls will be explained that this rule will prevent them from getting upset during the task. Girls will have to provide written informed consent for this part of the task separately before the task will start. In case of refusal, the PTT will not take place.

The researcher will stop the PTT immediately when the dyad starts discussing these problems and/or when the girls are clearly distressed or upset. The researcher will explain that the safety of the participants is most important and that the goal of the task is not to upset them or to discuss severe problems. The researcher will intervene by asking the girls how they are feeling, comforting them, and by offering them to take a break. If necessary, the girls can also seek comfort from their parents/main caretakers. Depending on how the girls feel after the break, the task will either be continued or terminated. This will be registered in the researcher’s logbook which is accessible across the team.

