When severe problems are discussed, or when the girls got upset, the coordinating researcher will immediately (by no contact within 24 h) contact the PI. The PI will contact the independent health care professional of Youz Rijnmond in case of severe problems. Depending on the situation, parents/main caretakers of both participants of the dyad or the teacher-mentor will be informed by the PI, depending on the specific topic the dyad discussed. The Principal Investigator will inform parents/main caretakers in situations of non-family-related acute problems and will advise them to contact the family doctor or the independent health care professional. In case of severe family-related problems, the PI will call inform the teacher-mentor. We will inform the mentor in case of family-related acute problems, so that the school will be able to decide to use the Veilig Thuis Protocol. In severe cases, the Independent Health Care Professional will also be consulted by the PI.

In all situations, we protect the privacy of all participants. This implies that we only should inform parents/main caretakers or the mentor more in depth when the participant initiated the conversation about suicide, self-injury, sexual or physical abuse, or eating disorders. In these cases, the dyad will be excluded from the study. In case of resistance during the task, study participation will also be terminated. This will be the case when (1) one of the participants behaves very upset; (2) the dyad will end up arguing; or (3) one of the participants within a dyad indicate that we need to stop video recording. The dyad will be excluded from the study and parents/main caretakers will be informed by telephone. After finishing the task, participants will be told that they can contact the independent health care professional when they feel upset. We will provide the telephone number of the independent healthcare professional.

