When girls talk about suicide, self-injury, sexual or physical abuse, substance abuse, or eating disorders during the online training sessions, the trainer will stop the session. In these cases, the coordinating researcher will immediately (by no contact within 24 h) contact the PI. The PI will contact the independent health care professional in case of severe problems. Depending on the situation, parents/main caretakers of both participants of the dyad or the school-mentor will be informed by the PI, depending on the specific topic. The PI will inform parents/main caretakers in situations of non-family-related acute problems and will advise them to contact the family doctor or the independent health care professional. In case of severe family-related problems, the PI will call inform the school-mentor. We will inform the mentor in case of family-related acute problems, so that the school will be able to decide to use the Veilig Thuis Protocol. In severe cases, the independent health care professional will also be consulted by the PI. In all situations, we protect the privacy of all participants. This implies that we only should inform parents/main caretakers or the mentor more in depth when the participant initiated the conversation about suicide, self-injury, sexual or physical abuse, or eating disorders. Girls will have to provide written informed consent for this part of the training separately before the PTT will start. The training sessions will be continued after this procedure.

All reported difficulties and support provided will be logged in the research team logbook. This part of the intervention protocol will be discussed and agreed with the headteachers/teacher-mentors of the participating dyads and will be explained in the participant information sheets for parents and girls.

Using the app

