## Discussion

The proposed study aims to provide insight into the short-term (T1, T2, T3 and T4) and long-term effects (T5) of the HFPM secondary school-edition prevention program on girls’ co-rumination, internalizing problems, wellbeing, and social-emotional behavioral functioning.

The HFPM program is school-based mindfulness and psychoeducation blended prevention program aimed at girls aged 13–15 years within secondary schools. This program was developed between 2020 and 2023 using the Intervention Mapping Approach for planning health promotion programs. The program comprises of 14 guided, weekly online lessons with mindfulness practices and psychoeducation, guiding the dyadic use of the application App yourself Happy. The goal of this program is to train 160 Dutch (80 dyads) high-risk girls between ages 13 and 15 to shift dyadic maladaptive ER patterns to more adaptive ER strategies within their dyadic interactions, while continuing to reap the benefits of their close, intimate friendships and exploring healthy, new alternatives for excessive co-rumination.

The objective of the HFPM cRCT is to evaluate the effectiveness of the prevention program HFPM, delivered by experienced mindfulness health professionals, compared with CAU and to unveil mechanisms of change. Self-reported risk for (early onset) depression and anxiety and self-reported and observed co-rumination will be the primary outcomes. Secondary outcomes will be self- and friend-reported friendship quality, self-reported positive and negative affect, self-reported interpersonal reactivity to personal distress, self-reported interpersonal responses to positive affect, self-reported anhedonic symptoms, self-reported mastery, and parent-reported health care use.

If the trial demonstrates that this prevention program is effective, secondary schools will be able to prevent excessive co-rumination in young adolescent girls and to improve girls’ short- and long-term mental health outcomes and friendship quality. The trial will also contribute to our understanding for whom, and under which circumstances, the prevention program is most effective, so schools will be able to match the intervention working mechanisms with the specific needs of subgroups of girls within schools. This knowledge will result in continuous improvements in the development of the train-the-trainer program, including training and supervision of HFPM trainers in order to maximize implementation quality and fidelity.

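### The protocol says observation data cannot be missing, but its own talk-task rules produce missing and cut-short records of a primary outcome, and it does not say how these are scored

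*Protocol article*

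**What the plan says.** Under *Handling of protocol non-adherence and missing data*, the protocol article first notes that online questionnaire items cannot be skipped, then adds: "Missing data during observations is also not possible". It assigns FIML to data missing in the follow-up period, such as missed waves and dropout.

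The *Discussion* confirms the status of the observed measure: "Self-reported risk for (early onset) depression and anxiety and self-reported and observed co-rumination will be the primary outcomes". It is taken at T0 and T4 from a task with 16 minutes of problem talk. *Coding process* gives the scoring: "Summed scores will be computed for each girl that are the total number of responses of each type that the adolescent produce". That section chooses totals over proportions deliberately, and the seconds spent on each problem topic are also summed.

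*Participation in the PTT* sets these rules:

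- On the separate consent for the task: "In case of refusal, the PTT will not take place".
- On content and distress: "The researcher will stop the PTT immediately when the dyad starts discussing these problems and/or when the girls are clearly distressed or upset".
- After a break: "the task will either be continued or terminated", with an entry in the researcher's logbook.
- After disclosure of listed severe topics: "In these cases, the dyad will be excluded from the study".
- If a girl is very upset, the pair argue, or one asks for recording to stop, participation ends and the dyad is excluded. *Objection by minors or incapacitated subjects* has a similar rule.

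*Withdrawal of individual subjects* adds that withdrawn subjects are not followed up. Data from earlier waves are removed only on explicit request.

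**The concern.** The missing-data section rules out something that the safety section provides for. Three consequences follow.

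1. **Cut-short records.** A count or a number of seconds from a shortened task is a real value on the wrong time base. Scored by the stated rule, it is too low, so a visibly distressed dyad could be recorded as co-ruminating little. FIML acts on absent values and leaves this one untouched.
2. **Absent records.** Severe problem talk and distress are plausibly related to co-rumination and depression. At T4 the triggers act after randomisation, in an open-label trial whose research staff know the allocation. FIML assumes that the observed data explain the missingness, and loss triggered by what is said during the task may break that assumption.
3. **Reach.** Observed co-rumination carries the second analysis of Hypotheses 1, 5 and 6. Observed topics and durations carry Hypotheses 8 and 9. If exclusion at T4 is handled like withdrawal, the dyad's T5 questionnaires are lost as well.

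**Working it through.** **1. The text.** No arithmetic is needed for the contradiction.

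| Event in the PTT rules | Record that results | Covered by the missing-data section? |
|---|---|---|
| Separate consent refused | None | T4 perhaps, through FIML; T0 is not follow-up |
| Stopped, then resumed | Interrupted | No |
| Stopped, then ended | Shortened | No |
| Dyad excluded | Unclear whether the partial record is kept; later waves probably lost | Later waves perhaps, through FIML |

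The rules also conflict with each other. After a stop for a severe topic the task may resume, yet dyads who disclose such topics are excluded. In addition, substance abuse is on the list of topics that stop the task but not on the list that directly precedes the exclusion sentence.

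**2. Effect of a shortened task.** At a constant rate, the score as a share of the full-task score is t/16:

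- 4 minutes: 25%
- 8 minutes: 50%
- 12 minutes: 75%

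If a share f of an arm's tasks stop at t minutes and those dyads talk at the average rate, the arm mean is 1 − f + f·t/16 of its full value. With an assumed f = 0.10 and t = 8, this is 0.90 + 0.05 = 95.0%. With t = 4 it is 92.5%, and with t = 12 it is 97.5%.

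**3. The plan's own sample size.** *Sample size calculation* gives 80 dyads for d = 0.50 with an intraclass correlation (ICC) of 0.20. Alpha and power are not stated in the article, so I assume two-sided 0.05 and 0.80. For m = 2 girls per dyad and J dyads, the noncentrality is λ = d√J / √(4(ICC + (1 − ICC)/m)), with J − 2 degrees of freedom. The denominator is √(4 × 0.6) = √2.4 = 1.549. The smallest J is 78, and J = 80 gives λ = 2.89 and power 0.814. The figure reproduces.

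For d = 0.35, 160 dyads give power 0.811. With 10% of dyads lost (144), power is 0.768; with 20% lost (128), it is 0.718.

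**4. Selective removal at T4, under assumed rates.** Let severity be standard normal in controls and shifted by −0.35 in the intervention arm. Both arms are cut at the same severity c. The outcome has a true d of 0.35 and correlates r with severity (0.4 to 0.6, assumed). With h(x) = φ(x)/Φ(x), the complete-case difference is

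0.35 − r·[h(c) − h(c + 0.35)].

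| Controls removed | c | Intervention removed | h(c) − h(c + 0.35) | r = 0.4 | r = 0.6 |
|---|---|---|---|---|---|
| 10% | 1.282 | 5.1% | 0.195 − 0.111 = 0.084 | 0.316 | 0.300 |
| 15% | 1.036 | 8.3% | 0.274 − 0.166 = 0.108 | 0.307 | 0.285 |

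The shift is 0.034 to 0.065 SD. The standard error of d with 160 dyads is √(2.4/160) = 0.122, so the shift is about 0.3 to 0.5 of one standard error.

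**5. Dependence on the assumptions.** Suppose removed dyads lie k SD above their own arm's mean. The difference then shifts by k·[f_C/(1 − f_C) − f_I/(1 − f_I)], where f_C and f_I are the shares removed. For 10% against 5%, this is 0.06 SD at k = 1 and 0.12 SD at k = 2. Equal shares at equal severity give no shift, and more removal in the intervention arm would reverse the sign.

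**The case against.** The sentence can be read narrowly: it follows a remark on skipped items, and the next sentence foresees missed waves and gives them to FIML. On that reading a lost T4 task is anticipated. This partly stands, but it does not rescue the statement. A shortened task is neither a skipped item nor a missed wave, and a lost T0 task is not follow-up loss.

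Other points for the plan stand:

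- Early losses are partly covered, because up to 16 dyads can be replaced between T0 and the end of Phase 1.
- The protocol cites earlier studies with the task as showing minimal risk, and girls are told beforehand which topics stop it. Stops may be rare.
- If exclusion also removes the partial record, shortened scores remain mainly for dyads stopped for distress without being excluded. How a stopped task is scored may be set out in the observation protocol or the SAP, which are not shown.
- The removal calculation is complete-case. The self-report analysis is a six-wave growth model under FIML, which keeps earlier waves and would recover part of the loss.

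A reader might also infer more than the documents support:

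- **That refusal singles out the worst-off dyads.** It is a declined consent before the task begins.
- **That the effect must be biased towards zero.** This requires fewer severe disclosures under the programme. The protocol itself notes that mindfulness practice can raise awareness of difficult experiences, so the opposite is possible.
- **That the rule for training sessions is a further contradiction.** After similar disclosures there, "The training sessions will be continued after this procedure". That rule governs a different procedure from the recorded task.

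**Conclusion.** The concern holds. The statement that observation data cannot be missing is wrong as written, and the scoring rule makes a shortened task score falsely low: about half at 8 of 16 minutes, assuming a constant rate and that the task is scored as it stands. FIML does not address this.

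The size and direction of any between-arm bias are unknown, because the documents give no rate of refusal, stopping or exclusion. The range of 0.29–0.32 for a true 0.35 rests on assumed removal of 10–15% of controls, an assumed correlation of 0.4–0.6, a common severity cut in both arms and a complete-case analysis. It is an illustration and does not estimate the bias under the planned models. The illustrated effect is modest, though power at d = 0.35 is only about 0.81 before any loss.

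The contradiction and the missing time base can be settled from the text alone. A claim that the trial's result will be attenuated cannot.

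**What to change.** 1. Delete or correct the sentence on observations, and say how refused, interrupted, stopped and excluded tasks enter the analysis.
2. Log the observed task minutes and the reason for any stop.
3. Analyse counts and seconds relative to observed time, for example counts with log minutes as an offset, or set stopped tasks to missing.
4. Keep all data already collected from every randomised dyad in the analysis unless removal is requested, as *Withdrawal of individual subjects* already allows.
5. Report refusals, stops and exclusions by arm and wave, with one sensitivity analysis for data missing not at random.
6. The investigators must reconcile the two statements in *Participation in the PTT* on what follows a stop for a severe topic: the task may continue, or the dyad is excluded. No stopping, exclusion or follow-up rule is proposed here.

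The cost is protocol and SAP wording, one logged duration, and one extra analysis. A logbook entry for stopped tasks is already planned and sessions are recorded, so no visits are added.

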##### Coding process

All video recordings will be stored and coded in Research Cloud. There will be three major aims of coding. The first is to provide information regarding the degree to which the girls participated in problem talk. The second aim is to provide information regarding how girls responded to friends’ statements about problems and/or worries. The third aim is to provide information about the topics on which girls co-ruminate. A team of two coders (both PhD students) will code the data. The coders will first obtain interrater reliability based on 25% of the interactions and then individually code the remaining interactions.

To determine how often girls participate in problem talk, all thought units that the girls produced will be coded as Own-Problem Statements, Friend-Problem Statements, or Non-Problem Statements. To do this, interactions in the PTT will be first transcribed by students of Developmental Psychology of VU Amsterdam and then segmented by the PhD students into thought units, or logical divisions of speech identified based on contextual and syntactic clues, such as pauses, changes in ideas, or changes in who was speaking [68, 69]. Coders will first classify all thought units according to whether they are Own-Problem Statements (i.e., statements about the speaker’s own problems) or not. Next, the thought units will be classified according to whether they are Friend-Problem Statements (i.e., statements about the speaker’s friend’s problems) or not. Each girl will be given a score for the total number of Own-Problem Statements, Friend-Problem Statements, and Non-Problem Statements that they produce.

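### Observation data are declared impossible to miss, yet the talk task can be refused, cut short or followed by exclusion, and raw totals have no rule for shortened tasks

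*Protocol article*

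**What the plan says.** All references are to the protocol article.

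- **Handling of protocol non-adherence and missing data:** "Missing data during observations is also not possible". The next sentence assigns FIML to data missing in the follow-up period, for example through an unavailable participant or dropout.
- **Negative and serious adverse events, Participation in the PTT:**
  - Girls give separate written consent. "In case of refusal, the PTT will not take place".
  - If the task does start, a stopping rule applies: "The researcher will stop the PTT immediately when the dyad starts discussing these problems and/or when the girls are clearly distressed or upset".
  - What follows such a stop is left open: "Depending on how the girls feel after the break, the task will either be continued or terminated". The outcome is entered in the researcher's logbook.
  - After certain severe topics: "In these cases, the dyad will be excluded from the study".
  - A separate rule deals with objection by a girl: "In case of resistance during the task, study participation will also be terminated". It covers a very upset girl, an argument, or a request to stop recording, and the dyad is then excluded.
- **T0 and T4 measures and Coding process:** dyads get 16 minutes. Each girl's score is her total number of own-problem, friend-problem and non-problem statements. For responses, "Summed scores will be computed for each girl that are the total number of responses of each type that the adolescent produce". Seconds per problem topic are also summed. Totals were chosen over proportions on purpose, because the cumulative experience of hearing responses is held to matter.
- **Discussion:** observed co-rumination is listed among the primary outcomes.

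**The concern.** The missing-data statement is a premise about a primary outcome, and the safety procedures in the same article contradict it. While the premise stands there is no reason to write a rule for a refused, stopped or excluded observation, and the article contains none.

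The reasons for loss are not neutral. They are visible distress and problem content, which lie close to what the task measures. Two kinds of harm are possible:

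- **Absent observations.** Refusal or exclusion removes dyads for outcome-related reasons, at T4 after randomisation.
- **Shortened observations.** A raw total over fewer minutes is lower, whatever the intensity of the talk. If such a total is kept, it looks like low co-rumination. FIML leaves it alone because the value is not missing.

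Observed co-rumination is the only primary outcome that is not self-report in an open-label trial. It feeds the observational models for hypotheses 1, 5 and 6, and observed topics and durations feed hypotheses 8 and 9.

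**Working it through.** The documents give no figure to reproduce here, so the main check is to set the sections side by side.

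**Step 1. What can happen to an observation**

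| Event | Stated consequence | Compatible with no missing data? |
|---|---|---|
| Separate consent refused | No task | No |
| Stopped, then continued after a break | Task resumes; total observed time not defined | Unclear |
| Stopped, then terminated | Incomplete recording | No |
| Suicide, self-injury, abuse or eating disorder raised | Dyad excluded | No |
| Resistance | Participation ended, dyad excluded | No |

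**Step 2. Who could be scored on a short task**

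The stop list and the exclusion list differ. Substance abuse is in the first and not in the second. The stop threshold is clear distress or upset, while the PTT section's exclusion threshold is a girl behaving very upset. The section on objection by minors gives a third threshold: merely looking upset is an example of resistance that ends participation. Depending on which section governs, the group terminated but not excluded ranges from very narrow to moderate. The article also does not say whether material recorded before an exclusion is kept.

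**Step 3. Effect on one score**

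At a constant rate of talk, share kept = minutes run / 16. Stops at 4, 8 and 12 minutes keep 4/16 = 25%, 8/16 = 50% and 12/16 = 75%.

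**Step 4. Effect on the arm contrast, if short counts are kept**

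Stop rates, stop times and the spread of the counts are not in the protocol, so everything here is assumed. With half the task lost on average, shift in SD = (net between-arm difference in share stopped) × 0.5 / CV.

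- Net difference 5%: 0.05 × 0.5 / 0.8 = 0.03 to 0.05 × 0.5 / 0.4 = 0.06 SD.
- Net difference 20%: 0.20 × 0.5 / 0.8 = 0.13 to 0.20 × 0.5 / 0.4 = 0.25 SD.
- Equal stopping in both arms: near zero by this formula.

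A simulation lets stopping depend on the amount of problem talk. Assumptions: full count with mean 100 and SD 40, true reduction 0.35 SD, logistic stop probability with slope 0.7 or 1.2 per SD, and stop time uniform over the task. Standardised effects:

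| Control tasks stopped | All truncated counts kept | Stopped tasks removed |
|---|---|---|
| 5% | 0.32–0.33 (6–9% lost) | 0.34–0.35 |
| 10% | 0.29–0.30 (13–17% lost) | 0.33–0.34 |
| 15% | 0.26–0.29 (18–25% lost) | 0.33–0.35 |

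Removal costs roughly 1–5% of the effect when standardised by the SD of the retained counts. Measured against the full-count SD of 40, the smallest value is 0.312, a loss of 1 − 0.312/0.35 = 11%.

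**Step 5. Effect on precision, if stopped dyads are lost**

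Inputs from the sample size section: 80 dyads per arm, d = 0.35, ICC 0.20 (stated there for depressive feelings, borrowed here). Two-sided alpha of 0.05 is assumed. Design effect = 1 + (2 − 1) × 0.20 = 1.2. Effective n per arm = 2 × dyads / 1.2. Power = Φ(0.35 × √(n/2) − 1.96).

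- 80 dyads: n = 133.3, power 81.5%.
- 5% lost, 76 dyads: 79.5%.
- 10% lost, 72 dyads: 77.4%.
- 20% lost, 64 dyads: 72.4%.

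**The case against.** A reader might infer that the plan analyses counts from stopped tasks as low co-rumination in the most distressed dyads. The documents do not say that. The exclusion rules would make most severe cases missing, not low, and the looser threshold in the section on objection by minors would widen exclusion further. The coding sentence, "All video recordings will be stored and coded in Research Cloud", tells us where recordings are kept and coded. It does not say that aborted tasks or excluded dyads are analysed. This part of the objection stands.

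The simulated losses also deserve little weight. Stopping is triggered by topic or visible distress, not by the number of statements. The protocol reports minimal risks in earlier studies with this task, which lends no support to a 15% stop rate. The simulation also ignores the planned adjustment for T0.

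The disputed sentence can be read more mildly, as meaning no gaps within a completed session, by analogy with questionnaires that do not allow skipped items. The FIML sentence may also cover a T4 session missed through dropout. Neither reading covers a refused or aborted task.

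Finally, the article reports only principal features and refers to a SAP that is not shown. Detailed scoring rules may be there, so their absence alone would be no finding. What remains is that the article states something its own procedures make untrue.

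**Conclusion.** The contradiction is certain: observations of a primary outcome can be absent or cut short, for reasons tied to distress and problem content. The scoring weakness is conditional. Raw totals over unequal observed time are not comparable, but this biases results only through shortened tasks that are neither excluded nor set to missing. Examples are termination for distress below the exclusion threshold, termination for substance abuse, or counts kept from before an exclusion.

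The size cannot be determined from the protocol. It is small if stops are rare or if stopped dyads are mostly excluded. The 6–25% loss is not an estimate for this trial. It needs stop rates of 5–15%, stopping linked to the amount of talk, and every truncated count retained. A bias towards no effect is likewise a possibility under those assumptions, not something the documents establish.

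**What to change.** 1. Delete the sentence that observation data cannot be missing, and reconcile that section with the PTT safety section and the section on objection by minors. The stop list, the exclusion list and the distress thresholds should be made consistent. Which rule applies is for the investigators; no change to the safety stopping rules is proposed here.
2. Record observed seconds for each task, net of breaks, in the logbook already kept.
3. Set scores from shortened, refused or excluded observations to missing and handle them with FIML, using T0 counts, self-reported co-rumination and CDI-2 as auxiliary variables where they are not already in the model.
4. Add a sensitivity analysis with observed time as exposure (a rate, or a log-time offset). It should not be the main analysis, because the protocol chose totals deliberately and a rate assumes that the unobserved minutes resemble the observed ones.
5. State whether data recorded before an exclusion are kept.
6. Report stops, refusals and exclusions by arm and wave, with stop times.

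The cost is one time field and a few sentences of text. The downside is slightly fewer observed scores and reliance on a missing-at-random assumption, which is open to doubt when distress drives the loss. The counts by arm let readers judge that.
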